**Methods/Design:**

HOLA is a multi-component, health promotion intervention funded by the National Institute of Mental Health (NIMH). This prevention approach will be tested against a *fotonovela*, an enhanced psychoeducation control condition, in a sample of Latino elderly with minor or subthreshold depression or anxiety. A total of 60 older Latinos (aged 60+) will be randomized to receive HOLA or the *fotonovela*. The primary outcomes of interest are recruitment, adherence, retention, and acceptability. Data will also be collected on: preemption of incident and recurrent major depression, generalized anxiety, and social phobia; reduction in depression and anxiety symptom severity; physical functioning; sedentary behaviors; social engagement; and self-efficacy.

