The third component consists of scheduling pleasant events. During the cool down phase of each walking session, the CHW will ask each participant to identify a pleasant event that they intend to do with another person before the next meeting. Individuals may choose to do this activity with another member of the group, with family, or with friends outside the group. The CHW will be trained to problem solve (for example, brainstorm) if a member of the group cannot think of a pleasant event. Subsequent sessions will start with participants reporting on how effectively they implemented their pleasant event plan while the CHW and the group provide positive reinforcement and feedback. This component provides a means to generalize the intervention into the participants’ everyday lives and relationships.

Mood ratings will be taken directly before and after each walk so participants can see, in real time, changes in their moods. A pedometer will be given to each participant prior to the first group walk, and will be used to track each participant’s progress and provide motivation. The group exercise will be carried out at a centrally located park that is owned and operated by the Miami-Dade County Parks and Recreation Department and is open to the public.

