#### Comparison condition: content and structure of enhanced psychoeducation through *fotonovela*

The *fotonovela* was chosen as a control condition over usual care because it is a health-related intervention in its own right and relevant to older mentally ill Latinos who may have low literacy [42]. *Fotonovelas* are booklets that use posed photographs and simple text bubbles to portray soap opera stories that convey educational messages. *Fotonovelas* differ from common educational materials in that they incorporate popular images, cultural norms, simple text, dramatic stories, and vivid pictures to raise awareness, promote health, and combat stigma [42, 43]. The *fotonovela* has not been shown to be effective in increasing mental health service use, nor has it been used as mental health treatment or as a prevention tool [43]. It, however, will help patients become aware of their condition.

Participants randomized to the enhanced psychoeducation will be given a copy of the theoretically informed and empirically grounded *fotonovela* developed by Cabassa and colleagues [44]. In addition, participants in the control condition will meet one month after they are given the *fotonovela* for an open forum to express opinions concerning the *fotonovela* as well as knowledge gained from reading the material. The PI, who is a clinical psychologist, will lead these discussion groups, which will consist of six control participants per group and last for an hour.

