### Measures and analysis

#### Feasibility objective: recruitment, randomization, retention, and acceptability

As a pilot study, the randomized prevention trial will examine feasibility. Consistent with recommendations from biostatistical workgroups funded by NIH [45], this pilot study is not powered to test a hypothesis. Successful recruitment will be defined as meeting 100 % of targeted randomization (n = 60), with 20 % or less of eligible subjects refusing randomization. Randomization will be deemed adequate if the randomization scheme produces equal numbers of participants randomized to each condition. Adequate retention will be defined as 85 % or more of randomized subjects completing the post-intervention assessment. Acceptability is defined as 80 % or more of sessions attended by subjects. Data will also be collected on the proposed outcome measures to be tested in a definitive randomized controlled trial.

Study measures will be administered at baseline, end of intervention, and at 6 and 12 months post intervention. Eligible participants will be paid $25 upon completion of assessments at baseline, the end of the intervention, at 6, and at 12 months post intervention for a total of $100. Trained research assistants (RA) will administer all of the assessments and will be kept blind to randomized study assignment.

After the baseline assessment, participants will be randomly assigned to the HOLA intervention or to the *fotonovela* condition. Randomization will be carried out using an automated program embodying the strategies of permuted block randomization.

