#### Study measures

In the full-scale trial the primary outcomes of this study will be the preemption of new and recurrent major depressive and anxiety disorders, as measured by the MINI [49], and change in depressive and anxiety symptom severity, as measured by the Quick Inventory of Depressive Symptoms, self-report (QIDS-SR) [51] and the Beck Anxiety Inventory (BAI) [52]. Both depression and anxiety episodes will be tracked because of their frequent co-existence as common mental disorders [53], and previous prevention trials have tracked both common mental disorders [54, 55]. Secondary outcomes of the full-scale study will include change in physical functioning, social engagement, and sedentary behaviors as measured by the WHO Disability Assessment Schedule (WHODAS 2.0) [56]; change in self-efficacy as determined with the General Self-Efficacy Scale [57]; and change in sleep quality using the Pittsburgh Sleep Quality Index (PSQI) [58].

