## Discussion

Many racial/ethnic minority elderly view traditional mental health services as highly stigmatizing [8, 59, 60]. Since health promotion/health behavior change interventions are culturally relevant [7] and effective in reducing risk factors [24, 29], they may be an optimal prevention strategy in the high-risk racial/ethnic minority elderly. This study will generate evidence of a potentially scalable intervention for depression and anxiety prevention in older Latinos in the midst of a rapid demographic transition. The use of a CHW delivering a health promotion intervention to prevent common mental disorders in Latino elderly is an innovative approach to reduce disease burden in a population living with high exposure to risk factors (comorbid physical and mental health conditions) and disparities in access to and engagement in mental health services [2–6]. Since increased physical activity and pleasant events are each effective in treating geriatric depression and anxiety [25–29], this study will determine whether an intervention that combines these two approaches will be acceptable, feasible, safe, and effective in preventing common mental disorders in older Latinos. By shifting the focus to prevention, and adding a CHW, two physical and social activation sessions, pleasant events scheduling, mood ratings, and pedometers, HOLA is an innovative and self-motivating intervention that makes efficient use of limited resources.

The integrated (mental and physical health) nature of this intervention enhances the innovation and potential clinical impact. In addition, the results of this study could also have implications for other high-risk, highly disadvantaged populations. Older African Americans have low rates of mental health service use [3], experience high stigma [59], and have high rates of co-morbidities [61]. Older Asian Americans also report high stigma [60] and are more likely to express distress through somatic symptoms rather than psychological terms. [62]. All of these groups could potentially benefit from the proposed health promotion intervention in the service of preventing common and disabling mental disorders. The development of a health promotion intervention designed to prevent common mental disorders could be a means of addressing multiple disparities (for example, mental health outcomes, mental health service use, stigma) among racial/ethnic minority elderly people.

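### Sedentary behavior is listed as a separate outcome, but its only named instrument is a disability schedule, so a difference on that schedule should not be reported as a difference in sedentary behavior (minor)

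*Protocol article*

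**What the plan says.** In the Abstract (Methods/Design), the non-primary data to be collected in this pilot include "physical functioning; sedentary behaviors; social engagement; and self-efficacy". Sedentary behavior is thus an item of its own, separate from physical functioning and from social engagement.

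The Study measures section is the only place that gives it an instrument. After the opening "Secondary outcomes of the full-scale study will include", it continues with "change in physical functioning, social engagement, and sedentary behaviors as measured by the WHO Disability Assessment Schedule" (WHODAS 2.0). No item, domain or sub-score is named for any of the three constructs.

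That section is worded for the later full-scale trial, but the Feasibility objective section carries the measures into the pilot: "Data will also be collected on the proposed outcome measures to be tested in a definitive randomized controlled trial". On timing it says: "Study measures will be administered at baseline, end of intervention, and at 6 and 12 months post intervention". No arm is excepted.

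The one activity device in the text belongs to the HOLA program: "A pedometer will be given to each participant prior to the first group walk".

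**The concern.** Difficulty in functioning and time spent inactive are different things. A person with no disability can sit most of the day. A disability score can also move for other reasons, such as mood, with no change in activity.

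Sedentariness is not incidental to this trial. The Background gives it as one reason why older Latinos are at risk, and group walking is a main component of HOLA. A statement that HOLA did or did not reduce sedentary behavior would interest readers and could shape the definitive trial. If the plan is followed as written, that statement would rest on a disability score. The result would be mislabeled, and the mismatch could be carried forward with the measure.

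**Working it through.** No formula applies, and the plan gives no figure to reproduce. The sample of 60 (30 per arm) is justified by feasibility and by similar pilots, not by a calculation. The check follows each mention of sedentary behavior, of the disability schedule and of any activity measure through the article.

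1. **Is sedentary behavior an outcome of this pilot?** Yes. The Abstract lists it, and the Feasibility objective section says the pilot collects the measures proposed for the definitive trial. The three specific aims in the Background do not name it.

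2. **Which instrument is named for it?** One, WHODAS 2.0 (Study measures). It is also the only instrument named for physical functioning and for social engagement, so three constructs share one schedule.

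3. **Could another measure in the text serve instead?**
   - The 10-meter walk test appears under Screening as a test of walking ability and sets exclusion limits in Table 1. It does not measure daily activity.
   - The pedometer is for tracking progress and for motivation, and the Discussion counts it among HOLA's components: "pleasant events scheduling, mood ratings, and pedometers, HOLA is an innovative and self-motivating intervention".
   - The control arm gets a booklet and one discussion group. The Comparison condition section begins "Participants randomized to the enhanced psychoeducation will be given a copy of the theoretically informed and empirically grounded" and mentions no device.
   - The QIDS-SR, BAI, General Self-Efficacy Scale, PSQI and MINI are assigned to symptoms, self-efficacy, sleep and diagnosis.

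   The number of activity or sitting-time measures described for both arms in the readable text is therefore 0.

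4. **Is disability a reasonable stand-in for sedentary behavior in this sample?** The entry criteria argue against it. Table 1 requires medical clearance for exercise, and it excludes people who cannot complete the 10-meter walk in under 23 seconds on average or who have significant symptoms during it. These rules select people who can walk, and being able to walk says little about how much someone walks.

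5. **How would the scores be used?** The Analysis section plans effect sizes and an intent-to-treat comparison of HOLA with the fotonovela for the outcomes of interest. Under the stated assignment, a WHODAS effect size would be reported under the sedentary behavior label as well as the other two.

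**The case against.** The strongest reply has four parts.

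- **The mismatch is inferred from the instrument's title.** The article reproduces no items, and the cited source is not available here, so a complete absence of sedentary content cannot be shown. This stands, and the conclusion is limited accordingly: the article gives no basis for the reading.
- **An article condenses the full protocol, and Fig. 2, the flow chart of screening and assessment, is not visible.** The abbreviation list defines T1 to T4, which appear nowhere in the readable text and may come from that figure. A further measure could be listed there. This also stands as a limit. But the article does state which instrument measures sedentary behavior, and the objection is to that stated assignment, not to missing detail.
- **The sentence concerns the full-scale trial.** This does not remove the point, because the Abstract and the Feasibility objective section bring the outcome and the measures into the pilot.
- **The outcome is non-primary in a feasibility pilot.** This stands and sets the severity.

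A reader might infer more than the article supports, in three ways. The first is that the arms cannot be compared at all. They can: the schedule is planned at all four assessments with no restriction by arm, and what lacks support is the meaning given to the comparison. The second is that giving pedometers to one arm blocks the comparison. The article never offers the pedometer as an outcome measure, so its use in HOLA alone shows only that it cannot fill the gap. The third is that the prescribed walking, 3 × 30 = 90 minutes a week, is the size of what goes unmeasured. That is a dose. Treating it as a between-arm contrast would assume full attendance, no walking by controls and no displacement of other activity, none of which the article states. Walking minutes are also not sedentary time.

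**Conclusion.** The point holds in a limited form and is minor. Sedentary behavior is a listed outcome whose only named instrument is a disability schedule shared with two other constructs, and the readable text describes no measure of activity or sitting time for both arms. A between-arm difference on the schedule can be estimated, but the article does not support calling it a difference in sedentary behavior.

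The effect is confined to one exploratory, non-primary outcome. Recruitment, adherence, retention and acceptability are unaffected, as is the use of the schedule for functioning.

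The conclusion rests on two assumptions: that neither the unseen figure nor the full protocol names another activity measure for both arms, and that the schedule has no separately scored sedentary content. If either is wrong, naming that measure or score in the text would settle the point.

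**What to change.** **Preferred: a change of wording.** Remove sedentary behaviors from the outcomes attributed to WHODAS 2.0 in Study measures and from the list in the Abstract, and report the schedule as disability or functioning only. This needs no new data and can be done although recruitment and delivery are under way (Trial status). The change should be dated and made before outcome data are examined. The cost is that the pilot then makes no statement about sedentary behavior.

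**Alternative: keep the outcome and measure it.** Add a short self-report question on daily sitting and walking time, asked identically in both arms at the existing assessments (baseline, end of intervention, and 6 and 12 months afterwards). This costs a few minutes per visit and a minor ethics amendment. Participants already enrolled would have no baseline value, so change from baseline could be computed only for those enrolled later.

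Under either option, pedometer counts should not be used as the between-arm measure, because the pedometer is described only as part of HOLA.

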#### Analysis

Univariate analyses will be conducted to determine if randomization yielded equivalent groups by comparing demographics, background factors, key outcome variables and important covariates and potential moderators at baseline using chi-square and *t*-tests. Confidence intervals will be examined for differences between group means for all measures as a means of summarizing these analyses. If systematic differences between the two groups are found, propensity score matching will be used in statistical tests of outcomes. As a preliminary evaluation of the interventions, effect sizes will be calculated to assess for evidence of potential effectiveness. However, we accept that the study will not be powered to provide strong evidence against the null hypothesis. An intent-to-treat analysis will be conducted for the outcomes of interest, comparing the participants who were randomized to HOLA with those in the *fotonovela* condition. These analyses permit the strongest inferences to be drawn regarding the effects of physical activity and enhanced psychoeducation, but as previously discussed they may be underpowered. For a more conservative assessment, an as-treated analysis will be conducted, comparing participants randomized to and completing HOLA to those randomized to the *fotonovela*. These analyses may provide a more sensitive measure of the true effect of HOLA on reducing depression and anxiety symptom severity.

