### Participants

The pilot study will randomly assign 60 older (60+) Latino participants with minor or subthreshold depression or anxiety to the HOLA intervention (n = 30) or enhanced psychoeducation (n = 30). The sample size is sufficient to provide meaningful data on the feasibility and the other outcome measures of interest. Additionally, this sample size is consistent with other pilot studies of physical activity interventions [38, 39]. Informed consent will be obtained from each participant. For a detailed description of the inclusion/exclusion criteria, see Table 1.

**Table 1 Tab1:** Inclusion/exclusion criteria

Inclusion criteria	Exclusion criteria
• Self-identify as Latino; • Age 60+; • Have minor depression as defined by a primary DSM-IV Axis I diagnosis of minor depressive disorder or subthreshold depression defined as a score ≥ 3 on the Patient Health Questionnaire (PHQ-2), OR subthreshold anxiety as defined as a score ≥ 3 on the Generalized Anxiety Disorder-2 scale (GAD-2); • Absent of episodes of major depression and anxiety disorders for past 12 months; • Volunteer informed consent; • Have medical clearance for participation in an exercise program by a physician, physician’s assistant, or nurse practitioner; • Agree not to use antidepressant medication (since these subjects could have a partially treated episode of major depression or anxiety and thus would be inappropriate for a prevention trial); • Expect to stay in Miami for the next 12 months	• Currently residing in a nursing or group home; • Have a terminal physical illness expected to result in their death within one year; • Have a diagnosis of dementia, comorbid diagnosis of dementia, or significant cognitive impairment; • Presence of any Axis I psychiatric disorder or substance abuse during preceding 12 months; • History of psychiatric disorders other than non-psychotic unipolar major depression or anxiety disorder; • High suicide risk; intent or plan to attempt suicide in the near future; • Taking cognitive enhancing medication or psychotropic medications (e.g., antidepressants); • Unable to complete 10-meter walk test in less than 23 seconds average; • Heart rate exceeds 170 beats per minute OR systolic blood pressure exceeds 180 during 10-meter walk test; • Chest or leg pain, dyspnea, dizziness, feeling faint, or other significant symptoms while completing 10-meter walk test; • Have contraindications to exercise outlined in the American College of Sports Medicine standards.

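### Baseline significance tests decide whether outcomes are tested by propensity score matching, a poor remedy for chance imbalance in a 60-person randomised trial

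*Protocol article*

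**What the plan says.** The Participants section fixes the size: "The pilot study will randomly assign 60 older (60+) Latino participants with minor or subthreshold depression or anxiety", 30 to each condition. Under the feasibility objective, "Randomization will be carried out using an automated program embodying the strategies of permuted block randomization", after the baseline assessment.

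The Analysis section then sets up baseline testing, using chi-square and t-tests, "to determine if randomization yielded equivalent groups by comparing demographics, background factors, key outcome variables and important covariates and potential moderators at baseline". Confidence intervals for differences between group means are to be examined as a summary. The consequence of a difference is stated as a rule: "If systematic differences between the two groups are found, propensity score matching will be used in statistical tests of outcomes". The same paragraph says: "An intent-to-treat analysis will be conducted for the outcomes of interest, comparing the participants who were randomized to HOLA" with those in the fotonovela condition.

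The article gives no significance level, number of baseline variables, propensity model, matching ratio, caliper or replacement rule. It names no baseline-adjusted regression and does not say how matching and intent-to-treat fit together.

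**The concern.** Three things look wrong, and none would be cured by supplying the matching details elsewhere.

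- After a sound random allocation, a significant baseline test is a chance finding. The tests therefore cannot show whether randomisation worked, yet they choose the outcome analysis.
- The choice depends on the data, so the method for testing the treatment effect is not fixed in advance.
- Matching is a tool for non-randomised comparisons. In a trial with 30 per arm, a form strict enough to improve balance drops randomised people, while a form that keeps everyone changes nothing.

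At stake is the preliminary evidence on depression and anxiety severity, functioning, self-efficacy and sleep. Aims 2 and 3 are to evaluate potential effectiveness on such outcomes, and the feasibility section says the outcome data are collected with a definitive trial in view.

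**Working it through.** **Inputs from the article.** 60 randomised, 30 + 30 = 60, by permuted blocks; baseline scores collected on all outcome scales; no power calculation to reproduce, since the study is declared not powered.

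**Inputs assumed.** Alpha 0.05; trigger = at least one significant baseline test; independent baseline variables; correlation ρ between baseline and follow-up score of 0, 0.3, 0.5 or 0.7; complete follow-up.

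**Step 1: how often the trigger fires by chance.** P = 1 − 0.95^k for k independent tests.

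- k = 5: 1 − 0.774 = 23%
- k = 8: 1 − 0.663 = 34%
- k = 10: 1 − 0.599 = 40%
- k = 15: 1 − 0.463 = 54%
- k = 20: 1 − 0.358 = 64%

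Correlated variables would lower these figures.

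**Step 2: what matching does once triggered.** Simulation, 2,500 triggered trials per setting, 30 per arm, no treatment effect, 5 or 10 normal baseline covariates of which the first is the baseline score of the outcome, and a logistic propensity score on all covariates. The outcome analysed is the follow-up score. Entries in the middle three columns are the mean squared error divided by that of ANCOVA on the baseline score. The last column compares caliper matching with regression on all the same covariates.

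| Covariates | ρ | 1:1, no caliper | 1:1, caliper 0.2 SD | With replacement | Caliper vs regression on same covariates |
|---|---|---|---|---|---|
| 5 | 0 | 0.97 | 1.62 | 2.04 | 1.39 |
| 5 | 0.3 | 1.15 | 1.62 | 2.25 | 1.43 |
| 5 | 0.5 | 1.60 | 1.71 | 2.37 | 1.49 |
| 5 | 0.7 | 2.74 | 2.05 | 3.05 | 1.79 |
| 10 | 0 | 0.97 | 1.79 | 2.48 | 1.44 |
| 10 | 0.3 | 1.11 | 1.91 | 2.67 | 1.53 |
| 10 | 0.5 | 1.36 | 2.04 | 3.08 | 1.61 |
| 10 | 0.7 | 2.25 | 2.28 | 3.99 | 1.78 |

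**Step 3: participants kept with the caliper.** On average about 18.2 pairs with 5 covariates and 16.6 with 10. Dropped: 60 − 2 × 18.2 = 23.6 and 60 − 2 × 16.6 = 26.8, or about 39% and 45% of those randomised.

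**Step 4: check by hand.** Losing people alone should inflate the variance by 60/36.4 = 1.65 and 60/33.2 = 1.81. In the simulation, ANCOVA applied within the caliper-matched sample gave 1.59 to 1.65 with 5 covariates and 1.81 to 1.89 with 10. So even the best use of the baseline score after matching does not recover what was dropped.

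**Step 5: the no-caliper case.** With 30 in each arm, 1:1 matching without replacement pairs everyone. The mean of the 30 pair differences equals the difference between the two arm means, whatever the pairing. The simulated ratios are identical to those of the unadjusted difference. No imbalance is corrected.

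**The case against.** The case for the plan is strongest on what a reader might infer beyond the text.

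- **That the plan certainly discards participants and contradicts intent-to-treat.** The article names no caliper or replacement rule, and matching 30 to 30 without a caliper drops nobody. The two analyses are left unreconciled; exclusions are not expressly planned. This stands. It does not rescue the rule, because the form that keeps everyone serves no purpose.
- **That variance roughly doubles.** That figure is not a property of this plan. It depends on the matching form, the caliper, the number of covariates and ρ, none of which is given. This stands, so only a range can be stated.
- **That the baseline scores go unused unless a test is significant.** The Study measures section describes the scale outcomes as changes, and a change score uses the baseline value. The unmatched change-score comparison has about 2/(1 + ρ) times the variance of ANCOVA, for example 2/1.6 = 1.25 at ρ = 0.6: less efficient, but not ignoring baseline.
- **That the trigger is any single p<0.05.** The article speaks of systematic differences and also looks at confidence intervals. The step 1 percentages are therefore illustrative. But these comparisons cannot tell a failed allocation process from chance, so a stricter reading of the word does not make the rule sound.
- **That the matching affects the trial's main conclusions, or certainly its effect sizes.** The primary outcomes are recruitment, adherence, retention and acceptability, which matching does not touch, and the study is openly unpowered. Matching is specified for tests of outcomes; the article does not say whether the effect sizes come from the matched sample.

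Matching details may properly sit in a fuller document. The rule that baseline tests select the outcome analysis is stated here, and those details would not change it.

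**Conclusion.** The point holds in a limited form. The plan lets chance baseline differences decide how outcomes are tested and prescribes a remedy that does not suit a 60-person randomised trial. With the assumed 0.2 SD caliper, matching loses about 23 to 27 of 60 participants and has 1.6 to 2.3 times the variance of ANCOVA on the baseline score, or 1.4 to 1.8 times that of regression on the same covariates. Without a caliper it gives back the unadjusted difference. Across the matching forms and ρ from 0 to 0.7, the ratio to ANCOVA runs from about 1.0 (no caliper, uninformative baseline) to 4.0 (with replacement, 10 covariates, ρ = 0.7).

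These figures rest on independent normal covariates, complete follow-up and analysis of the follow-up score. Severity is moderate: the rule bears on secondary, preliminary evidence of potential effectiveness, and leaves the feasibility criteria intact.

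**What to change.** In the Analysis section:

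1. Delete the baseline tests as a trigger, and delete the propensity score matching. Report baseline characteristics by arm descriptively.
2. For the continuous outcomes (QIDS-SR, BAI, WHODAS 2.0, General Self-Efficacy Scale, PSQI), prespecify the HOLA minus fotonovela difference from ANCOVA, or from a repeated-measures model over the three follow-ups, adjusted for the baseline score of that outcome. Analyse by randomised arm, using all randomised participants with follow-up data. At the 85% retention target 0.85 × 60 = 51 would have a post-intervention score, so up to 9 might not; the repeated-measures model accommodates missed visits.
3. For incident or recurrent disorder on the MINI, compare proportions by randomised arm. Entry requires absence of major depression and anxiety disorders for the past 12 months, so there is no baseline value of that outcome to adjust for.

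The cost is analysis wording only. The baseline scores are already collected, and no visit, measure or sample size changes. The change should be made before outcomes are analysed by arm.
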